## Abstract

**Background:**

Children with conduct problems vary considerably in how they respond to behavioral interventions. Although group-based, child-focused programs are increasingly implemented, research still relies on retrospective parent or teacher reports and group-level outcomes. These traditional approaches often obscure individual differences in treatment response and reduce the potential for individualized behavioral support tailored to each child’s unique profile. The Dino Study—Daily Intervention-based research on Nurturing Opportunities—introduces the Incredible Years Dinosaur Program in the Netherlands for children aged 4–8 with conduct problems. This evidence-based program, grounded in cognitive-behavioral principles, aims to strengthen children’s emotional regulation, social skills, and problem-solving through structured, play-based group sessions. However, little is known about mechanisms of change in children’s daily life, particularly how emotional and behavioral improvements unfold within and across individual children during intervention. This study evaluates the program’s effectiveness in reducing externalizing behavior and promoting cognitive and prosocial functioning, and explores daily variability in children’s emotional and behavioral responses using a daily diary design.

**Methods:**

This protocol outlines a randomized controlled trial with a waitlist control condition. A total of 120 children will be randomly assigned (1:1) to the intervention or waitlist group. Participants will be recruited via professional institutions and primary schools in both preventive and clinical contexts. In addition to pre- and post-assessments, Intensive Longitudinal Data (ILD) will be collected to capture daily fluctuations in mood, behavior, and family interactions before, during, and after the intervention. This design enables analysis of group-level effects as well as intra-individual change patterns.

**Expected outcomes:**

Findings will offer novel insights into how children respond individually to structured interventions in real-life settings and inform more personalized, ecologically valid approaches to early behavioral support.

**Trial registration:**

ClinicalTrials.gov (NCT07051642).

## Introduction

Over the past decades, behavioral interventions for young children have primarily focused on improving parenting practices, based on the assumption that child outcomes are best enhanced by modifying caregiver behavior [1,2]. While such parent-directed approaches have yielded meaningful results, they also highlight a striking limitation: the relative lack of focus on the child as an active agent in the process of change [3,4]. This is particularly problematic for young children with conduct problems, as their heightened difficulties with emotion regulation, social functioning, and adaptive coping make them especially vulnerable in everyday situations [5,6]. At the same time, not all children with behavioral difficulties require the same level of support, highlighting the need for an individualized approach. While some demonstrate resilience and adapt effectively to everyday challenges with limited external support, others appear more sensitive to contextual stressors and benefit from structured, consistent behavioral guidance. However, large-scale intervention programs rarely account for individual differences in responsiveness, and instead evaluate outcomes based on group-level averages [7,8]. Such an approach risks overlooking children who deviate from the average trajectory, including those who derive substantial benefit from the intervention, as well as those who experience little to no improvement. This issue has been recognized in clinical research, prompting a shift toward evaluating personalized intervention outcomes, investigating who benefits most under which conditions, and uncovering the mechanisms by which change occurs [9].

Recent methodological advances offer tools to better capture individual variability in intervention outcomes. In particular, daily diary approaches—drawing on intensive longitudinal data (ILD)—allow researchers to examine short-term fluctuations in children’s emotional and behavioral states across everyday contexts [10,11]. These methods enable a more dynamic and ecologically valid understanding of how interventions are experienced in real time. While variability in child outcomes has been described in earlier studies, most rely on retrospective parent reports or pre-post comparisons, which mask within-person processes and delay the detection of early signs of change [10,12]. This constrains the development of interventions that are attuned to individual developmental trajectories and responsive to early, intra-individual signals of change.

Emerging insights from the Environmental Sensitivity Framework [13]—a synthesis of multiple theoretical models including Differential Susceptibility [14], Vantage Sensitivity [15], Biological Sensitivity to Context [16], and Sensory Processing Sensitivity [17]—suggest that individuals differ in their responsiveness to environmental influences. Children who display greater emotional reactivity or baseline environmental sensitivity may be more responsive to environmental input, including interventions. That is, children who show more day-to-day variability in affect may benefit more from structured, supportive programs in the environment than their less reactive peers. In the context of behavioral problems, emotionally sensitive children may particularly lack the regulatory tools to manage negative affect, making them more vulnerable to emotional escalation during daily challenges [18]. While the Environmental Sensitivity Framework encompasses heightened responsiveness to both negative and positive input, this sensitivity may initially manifest as greater reactivity to stress or frustration. This is particularly the case for children who have not yet developed adaptive coping strategies. Taken together, these insights highlight the need for intervention studies that not only evaluate overall effectiveness, but also examine individual sensitivity and the dynamic processes and mechanisms through which change occurs.

The address this need, the present study evaluates the effectiveness of the Incredible Years (IY) Small Group Dinosaur Child Program, a structured, child-focused intervention aimed at improving children’s emotional regulation, social functioning, and academic-related skills, and at reducing externalizing behavior [19–21] in the Netherlands. The program includes 18 weekly group sessions using playful, dinosaur-themed materials and has demonstrated effectiveness in both clinical and community contexts across countries such as the United States, Canada, and Spain [22–25]. The primary objective is to assess overall program effects on children’s emotional, social, and cognitive development through a randomized controlled trial. In addition to this broad evaluation, the study also incorporates daily diary methodology to examine real-time fluctuations in children’s emotions and behavior, individual sensitivity profiles, and daily parent–child dynamics throughout the intervention period. Through this dual approach, we aim to identify not only variability in outcomes, but also potential mechanisms of change that unfold in daily life. Importantly, this is the first study to combine a randomized controlled trial of the Dinosaur Program with daily diary assessments. This design captures how children respond to the intervention in their everyday environments.

By collecting daily data on emotions, behaviors, and parent–child interactions, the ILD design not only identifies day-to-day variability but also provides insight into emotional sensitivity, behavioral adaptation, and relational patterns over time. Grounded in the Environmental Sensitivity Framework, the study operationalizes emotional sensitivity as moment-to-moment fluctuations in negative affect prior to the intervention, based on empirical indicators derived from daily diary reports. This framing allows us to explore whether children with higher baseline sensitivity respond differently to the intervention. Beyond identifying individual variability, daily diary data offer a window into potential mechanisms of change. Since interventions such as the Dinosaur Child Program aim to influence not only behavior but also emotion regulation and relational dynamics, it is crucial to understand how these processes unfold in the flow of everyday life. By tracking moment-to-moment affective and interpersonal shifts, we can reveal dynamic pathways of change, such as improved co-regulation or reduced emotional escalation. This process-level insight supports a shift from outcome-based evaluation to more personalized, mechanism-informed intervention strategies. Finally, the study examines how family micro-dynamics contribute to intervention outcomes. Because children’s behavior emerges through daily caregiver interactions, ILD enables analysis of these dynamic exchanges over time. Understanding real-life family processes underlying intervention effects is essential for advancing personalized child mental health care and tailoring support to individual needs the field of personalized child mental health care.

### Study aim and research questions

The overarching aim of this study is to evaluate the effectiveness of the Dinosaur Child Program in reducing externalizing behavior and improving emotional and social functioning in children aged 4–8. Furthermore, the study aims to explore individual variability in intervention response and real-time parent–child dynamics using the daily diary methodology.

Specifically, the following research questions and hypotheses are addressed:

1. **Does participation in the Dinosaur Child Program lead to greater improvements in children’s emotional, social, and cognitive functioning, and reductions in externalizing behavior compared to a waitlist control group?**

*H1*: We hypothesize that children in the intervention group will show significantly more improvement in teacher- and parent-reported social, emotional, and cognitive/linguistic competencies, and significantly greater reductions in externalizing behavior than children in the control group.

2. **Does the intervention lead to reduced emotional variability and fewer daily behavior problems, as captured through daily diary methodology?**

*H2*: We hypothesize that children in the intervention group will exhibit fewer and less intense fluctuations in negative affect (controlled for mean level changes) and fewer moments of defiance, tantrums, or other behavior problems across the day, compared to the control group.

3. **Does the intervention alter day-to-day parent–child dynamics by reducing children’s experience of negative affect and promoting shared positive affect in interaction with their parents?**

*H3*: We hypothesize that children in the intervention group will show fewer escalations of negative affect and more intense shared positive moments with their parents than those in the control group. These effects are expected to be most pronounced in children who show higher baseline emotional sensitivity, operationalized as greater moment-to-moment fluctuations in negative affect prior to the intervention.

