## Materials and methods

### Study design

This protocol, which adheres to the SPIRIT 2013 guidelines (see S1 File), describes the Dino Study (Daily Intervention-based research on Nurturing Opportunities), a two-arm randomized controlled trial (RCT) designed to evaluate the effectiveness of the IY Small Group Dinosaur Child Program in Dutch children aged 4–8 years with perceived elevated or (sub)clinical levels of conduct problems [20,21,24]. A total of 120 children and one primary caregiver per family will be enrolled and randomly assigned to either an intervention group (n = 60) or a waitlist control group (n = 60), using a 1:1 ratio. The study assesses both group-level effects and individual variability in treatment response by analyzing intensive longitudinal data (ILD) from daily diaries to capture children’s moment-to-moment negative affect, externalizing behaviors, and daily parent–child interactions. The intervention group will receive the Dinosaur Child Program in small groups across 18 weekly sessions. The control group will receive care-as-usual and will be offered the intervention after posttest assessment. Pretest (T1) and posttest (T2) assessments will be conducted using standardized questionnaires and a brief child interview, with T2 scheduled 19 weeks after T1. In addition, daily diary data on children’s emotional states, behavior problems, and parent–child interactions will be collected via the m-Path application [26] during a one-week baseline period, the 18-week intervention, and a one-week follow-up (i.e., 20 weeks total). Parent and child will complete the diary jointly each evening (Fig 1). Eligibility criteria include: (a) child age between 4 and 8 years at the start of the study (September 2025), (b) parental indication that the child shows elevated or (sub)clinical levels of conduct problems in daily life (e.g., frequent defiance, aggression, or rule-breaking behavior), (c) daily contact between the child and the participating parent, and (c) sufficient fluency in Dutch. Children are excluded if they have an intellectual disability (IQ < 70) or insufficient Dutch language proficiency.

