#### Child emotional variability.

Emotional variability will be operationalized using parent–child dyadic daily assessments collected via the m-Path app [26]. Each evening, parents and children will complete a short diary survey including 2–3 emotion-related items (e.g., “Did your child experience strong emotions today?”) on a 5-point scale (1 = “not at all” to 5 = “very much”). Variability will be calculated based on within-person standard deviations, and changes over time will be explored using a moving window approach [28].

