#### Daily diary-based outcomes.

***Emotional variability and behavior problems (Secondary outcomes; RQ2).*** To capture within-person variability in emotional and behavioral functioning, daily diary surveys will assess both emotional functioning and behavior problems, completed each evening by the parent–child dyad using the m-Path app [26]. Emotional variability will be measured using a set of seven momentary emotion items derived from the Positive and Negative Affect Schedule for Children (PANAS-C) [29] and the original PANAS [30]. Children will indicate how they felt “at the moment” on a 7-point scale ranging from 1 (*not at all*) to 7 (*very much*), for the emotions proud, happy, calm, ashamed, sad, angry, and tense. To enhance developmental appropriateness and alignment with the Dinosaur Child Program, each response option is accompanied by a visual cue: a small-to-large image representing the intensity of each specific emotion, consistent with the emotion cue cards used during the intervention. Behavior problems will be assessed with three items reflecting hostility-related externalizing behaviors, adapted from the externalizing spectrum framework [31]. These include losing one’s patience, saying something mean to someone, and being angry or aggressive towards someone. Responses will be recorded on a 5-point Likert scale ranging from 1 (*not at all*) to 5 (*very often*), allowing for sensitive detection of daily fluctuations in child behavior over time.

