### Statistical analysis

All data will be analyzed using R [50] and Mplus [51]. Each family will be assigned a unique study ID to ensure anonymized data handling. Statistical analyses will follow a staged approach, aligned with the study’s three hypotheses. Missing data will be handled using full information maximum likelihood estimation within Latent Change Score (LCS) and multilevel models, minimizing bias due to attrition or intermittent missingness. Sensitivity analyses, including intention-to-treat analyses that incorporate all randomized participants regardless of adherence or dropout, will be performed to assess the robustness of the findings. Additional subgroup analyses exploring moderators such as child age, gender, and baseline severity will be conducted to evaluate consistency of intervention effects.

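### H3's baseline sensitivity moderator, read as a within-child SD of negative affect, is not separated from the child's mean level, so a benefit that depends on level could be read as a sensitivity effect

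*Protocol article*

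**What the plan says.** The Introduction of the protocol article says that "the study operationalizes emotional sensitivity as moment-to-moment fluctuations in negative affect prior to the intervention". H3, under Study aim and research questions, repeats this for the moderator: effects should be strongest in children with "higher baseline emotional sensitivity, operationalized as greater moment-to-moment fluctuations in negative affect prior to the intervention".

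The index comes from the Moderators part, under Child emotional variability: "Variability will be calculated based on within-person standard deviations". The ratings are bounded. That section describes 2-3 items scored 1 to 5, while Daily diary-based outcomes describes seven emotion items on a "7-point scale ranging from 1 (*not at all*) to 7 (*very much") format. Study design sets the diary periods as "during a one-week baseline period, the 18-week intervention, and a one-week follow-up", with one entry each evening, so the baseline SD rests on at most 7 reports.

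Level is mentioned in two other places. H2 predicts "fewer and less intense fluctuations in negative affect (controlled for mean level changes"). Statistical analysis adds: "Additional subgroup analyses exploring moderators such as child age, gender, and baseline severity will be conducted". The Hypothesis 3 analysis section names time-by-condition terms and mentions neither a sensitivity term nor a baseline-mean term.

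**The concern.** On a bounded scale the SD is not free of the mean. A child who almost always gives the lowest rating cannot show a large SD. Near the floor, children with a high baseline SD are therefore largely those with a high baseline mean. If the program helps children more when they start with more negative affect, an SD-by-condition interaction can appear even when all children have the same underlying variability.

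That children with more negative affect gain more, and that more reactive children gain more, are different conclusions. Only the second supports the Environmental Sensitivity account on which the Introduction and Discussion build the question of who benefits. As described, the moderator cannot tell them apart. H2 shows that the authors see a need to separate fluctuation from level, yet H3 has no matching step for the moderator.

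**Working it through.** **The plan's own figures.** The article gives no number for the H3 moderator. Its only between-person calculation, 64 per group for d = 0.5 and 26 per group for d = 0.8 (alpha 0.05, power 0.80), is reproduced exactly by a two-sided two-sample t-test. It does not bear on this point.

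**Inputs from the article.** 120 children, 60 per arm; at most 7 baseline evenings; ratings on 1-7 or 1-5; a within-child SD as the index.

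**Inputs assumed.** The level and spread of negative affect, the true within-child SD, and the way benefit depends on level. The article gives none of these.

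**Step 1: why SD and mean are tied.** For ratings between a and b with mean m, the SD (divisor n) cannot exceed √[(m − a)(b − m)].
- On 1-7: at m = 1.5 the ceiling is √(0.5 × 5.5) = 1.66; at m = 4 it is √(3 × 3) = 3.
- On 1-5: at m = 1.5 it is √(0.5 × 3.5) = 1.32; at m = 3 it is √(2 × 2) = 2.

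**Step 2: benefit that depends on level, generic outcome.** 2000 simulated trials per setting; four items on 1-7, rounded and clipped; 7 evenings; latent between-child SD 1.0; the same latent within-child SD of 1.2 in every child. The treatment effect is moderated only by the latent mean, by 0.3 or 0.5 outcome units (residual SD 1) per SD of that mean. The table shows how often SD × condition is significant (two-sided, nominal 5%); paired values are for 0.3 / 0.5.

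| Latent mean | Correlation of SD and mean | SD × condition alone | + mean | + mean and mean × condition |
|---|---|---|---|---|
| 1.0 | 0.79 | 23.6 / 53.3% | 23.4 / 53.2% | 6.0 / 6.4% |
| 1.5 | 0.72 | 19.4 / 44.6% | 20.0 / 44.8% | 4.8 / 5.9% |
| 2.0 | 0.62 | 15.0 / 32.6% | 15.9 / 32.8% | 4.6 / 5.7% |
| 3.0 | 0.32 | 7.6 / 12.8% | 8.0 / 13.4% | 4.5 / 4.9% |
| 4.0 | 0.00 | 5.5 / 4.1% | 5.4 / 4.3% | 4.8 / 4.3% |

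With no moderation by level, SD × condition alone stays at 4.8-5.3%. The main effect of the mean removes nothing; the mean-by-condition term does the work. The simulation error at 5% is √(0.05 × 0.95 / 2000) = 0.5 points, so 6.4% at latent mean 1.0 hints at a small remainder very close to the floor.

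With three items on 1-5, the correlation is 0.67 at latent mean 1.5 and 0.50 at 2.0. The directional false rate (nominal 2.5%) is 16-35% and 11-22%, and 2-3% after both mean terms are added. The mechanism therefore holds on either scale.

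**Step 3: what this means for particular outcomes.** Directional rates, nominal 2.5%, with the same true variability in every child:
- *Outcome on the same negative-affect items, 25% or 40% proportional reduction for all:* 17-55% at latent mean 1.5-2.0, 9-32% at 2.5, 4-14% at 3.0. With both mean terms, 0-3%.
- *Single 1-5 anger item, as in H3's conflict measures:* about 8-17% near the floor. Another run (correlation 0.5 with negative affect, 25-40% proportional reduction) gave 4.5-15% at mean 1.5-2.0 and 4-8% at 2.5-3.0.
- *Nice-moments item, correlation −0.4 with negative affect, uniform benefit:* 2.5-3.7% at every mean, essentially nominal.

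**Step 4: cost of the correction.** With a true sensitivity effect only, power without and with the mean terms was 0.78 and 0.74, 0.75 and 0.65, and 0.50 and 0.50 in three settings.

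**The case against.** The strongest reply is that the article does not write out a sensitivity-by-condition model at all, so its covariates may be left to a fuller document. That holds for the model, and the missing interaction term is not the point here. But the article does fix the construct and an index for it, and states level control for H2 only. Followed as written, the moderator mixes level with sensitivity.

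Second, the link between the SD and H3 is inferred. The Child emotional variability section names neither H3 nor negative affect, its example item concerns strong emotions in general, and the Moderators introduction lists emotional sensitivity and daily fluctuations separately. This stands as a caveat. The section's place under Moderators and the shared idea of fluctuation make the reading strong, but it is not an explicit statement.

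Third, a reader might take the 17-55% as the error rate for H3. The documents do not support that. H3 concerns escalations of negative affect and shared positive moments with parents, measured partly by other items, and Step 3 shows much smaller rates or none. The higher figures in Step 2 assume moderation by level of a chosen strength.

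Fourth, no expected level of negative affect is given, and children are selected for conduct problems, so a floor cannot be presumed. This stands.

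Fifth, H2's control concerns change in the outcome over time, not differences between children at baseline. The parallel is therefore imperfect, but it shows the same concern about level.

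Sixth, level may be part of the construct, since the Introduction allows that sensitivity first shows as stronger reactivity to stress. CBQ Negative Affectivity and baseline severity are also planned moderators. But neither is stated to be fitted jointly with the SD, and separate tests of correlated moderators cannot separate them.

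**Conclusion.** The point holds in a conditional form. Reading the Moderators section together with H3, the sensitivity moderator is a within-child SD from at most 7 bounded ratings, with no separation from the mean. If negative affect lies near the floor and benefit depends on level, a level effect could be reported as sensitivity.

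Under assumed inputs the SD-mean correlation near the floor is about 0.5-0.7. The false directional rate against 2.5% is roughly 8-17% for an anger-type item and up to about 50% for an outcome on the same negative-affect items. It is nominal for shared positive moments with uniform benefit, and the problem disappears at mid-scale.

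A reader might infer that the trial will report a false sensitivity effect. The article does not support that, because it gives neither the level of negative affect nor the form of any benefit. H3 is a secondary question and the comparison of arms for RQ1 is unaffected. This is a worthwhile, inexpensive improvement to the conclusion about who benefits.

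**What to change.** In H3 and under Child emotional variability, state that the moderator is tested net of level. Enter baseline-week mean negative affect and its interaction with condition (and time) beside the baseline SD and its interactions, or use a mean-corrected variability index. The mean as a main effect alone is not enough. Interpret only the SD interaction that remains as sensitivity. The same edit should name the items and scale that form the moderator, since the two diary descriptions differ.

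The cost is a wording change and one extra covariate with its interactions, from diary data already planned. The downside is some collinearity and a modest loss of power for a true sensitivity effect, at most about 10 points in the settings tried (0.75 to 0.65).
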